### Control Condition

Participants assigned to the control condition will receive a link to a website with resources similar to those provided at the end of the BRAVE intervention. On the site, veterans are able to find care centers, peer support groups, and veterans service organizations by clicking through the organized content. Participants will be asked to explore the content on the website for about 20 to 30 minutes, to match the length of the BRAVE intervention. They can return to the website at any time. After each follow-up survey, the control participants will be sent the link to these resources again to have it easily accessible.

### Measures

#### Overview

Measures will be collected at screening, baseline, and all follow-up time points through confidential web-based surveys. After completing the screening survey and becoming enrolled, participants will receive a US $20 gift card for each survey they complete (a total of US $100 for all surveys).

#### Demographics and Background

Participants will fill out several demographic items that will be used to describe the sample. These include age, sex at birth, gender, race, ethnicity, income level, military branch, military rank and pay grade at discharge, number and location of deployments, education level, marital status, and number of children. Participants will also complete a measure of combat exposure to assess for presence and severity of combat experiences while in the military [27].

#### Primary Outcomes

Primary outcomes are drinking behavior (past 30-day frequency, quantity, and number of binge-drinking days), negative alcohol-related consequences, and treatment initiation. Three past 30-day drinking outcomes will be assessed through single-item self-reports: drinking days, average drinks per occasion, and binge drinking days. Alcohol-related consequences in the past 30 days will be assessed with the Short Inventory of Problems [68], which is modified from the Drinker Inventory of Consequences [69]. The treatment outcome will be measured as treatment initiation in the time period after the intervention (ie, post baseline). Treatment initiation is assessed with an item asking participants to indicate if they have seen a provider at a VA or non-VA care setting for therapy, counseling, support groups, hospitalization, or medications for any concerns related to alcohol or substance use (eg, if they sought help to drink less, or attended groups to stay abstinent from cannabis or other drugs) or mental health concerns (eg, to help with stress, anxiety, depression, nightmares) in the past 6 months (at baseline) and past 3 months (follow-ups). Providers are defined for participants as a mental health or behavioral health provider (eg, psychiatrist, psychologist, social worker, mental or behavioral health nurse, or other providers), a general medical provider (eg, primary care doctor, physician assistant, and nurse practitioner), or an addiction specialist (eg, addiction counselor). Care is specified as either in-person or via telehealth.

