## Introduction

### Background

Americans who served in the US military during or after September 11, 2001, and have since been discharged (post-9/11 veterans) experience concerning rates of mental health disorders, with an estimated prevalence of depression and posttraumatic stress disorder (PTSD) ranging from 10% to 30%, respectively [1-5], and often co-occurring [6]. Alcohol use disorder (AUD) is the most common substance use disorder among veterans [7-10] and it, too, often co-occurs among veterans with depression or PTSD [11-14]. Approximately 1 in 10 post-9/11 veterans who are seeking any care within the Veterans Health Administration meet the criteria for an AUD [9], and studies show that upwards of 40% of these veterans drink alcohol at levels that place them at risk for negative alcohol-related consequences (ie, hazardous drinking) [10,15-18]. Veterans younger than 40 years old drink more heavily than older veterans [9,10] and may be at heightened risk for developing an AUD later in life, making early intervention and prevention efforts for younger adult veterans essential.

Despite the availability of evidence-based behavioral health care (ie, care for mental health or substance use disorders) through Veterans Affairs (VA) and in private care settings [19-22], not all veterans with behavioral health needs use these services. Estimates suggest that over 50% of post-9/11 veterans meet screening criteria for a mental health disorder (including AUD), but less than half receive care [23-29]. Those who do often receive inadequate care to address their needs, such as seeing a mental health provider only once or twice for an intake without follow-up or not completing a doctor’s full planned prescription for psychotropic medications [30-32]. Veterans who engage in heavy drinking and have a co-occurring PTSD and depression diagnosis have particularly difficult barriers to seeking care [33]. It is important to target heavy alcohol use early after discharge and in young adulthood so both alcohol use and co-occurring mental health problems do not become chronic or more difficult to treat.

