### Participant Recruitment and Eligibility

The BRAVE intervention is designed for mobile phones with internet capabilities and is targeted toward young adult veterans. Though the intervention is designed for use on mobile phones, it can be accessed through computers and tablets. Given the focus on a younger veteran cohort, eligibility criteria include (1) US veteran who has been discharged or separated from the Air Force, Army, Navy, Marine Corps, or Coast Guard (participants could have also been in the reserves or guard units, but not on active duty), (2) between the ages of 18 and 40 years, (3) a score on the 10-item Alcohol Use Disorders Identification Test (AUDIT [54]) of 4 or greater (men) or 3 or greater (women), which represents cutoff scores to identify those who may benefit from interventions to reduce alcohol misuse, (4) no upcoming appointments at the VA or elsewhere to receive treatment for a behavioral health concern (such as depression, PTSD, or alcohol use concerns), and (5) no appointments in the past six months for behavioral health treatment at a VA or elsewhere. The purpose of these latter 2 criteria is to reach participants outside of traditional care settings (ie, those who may need care but who are not receiving it) and to measure the effect of the intervention on treatment initiation. Participants also need access to the internet via a computer, tablet, or phone; a working email address; and the ability to read and understand English. Based on these criteria, we will recruit 800 participants who will be randomly assigned to the BRAVE intervention (n=400) or a resources-only control condition (n=400) that presents resources for care seeking (eg, location of local VA and links for connecting with local veteran service organizations) without any personalized content.

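### The entry screen and the treatment-initiation item are not worded to match, and no use of the baseline answer is stated, so care already under way can be counted as initiation

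*Protocol article*

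**What the plan says.** **Entry (Participant Recruitment and Eligibility).** Two criteria concern care. One is "no upcoming appointments at the VA or elsewhere to receive treatment for a behavioral health concern". The other is "no appointments in the past six months for behavioral health treatment at a VA or elsewhere". The section says that they serve to reach "those who may need care but who are not receiving it) and to measure the effect of the intervention on treatment initiation".

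**Outcome (Primary Outcomes).** The item asks participants "if they have seen a provider at a VA or non-VA care setting" and lists the kinds of care: "for therapy, counseling, support groups, hospitalization, or medications for any concerns related to alcohol or substance use". Mental health concerns such as stress or anxiety count as well. Participants are told which providers qualify, and the list includes "a general medical provider (eg, primary care doctor, physician assistant, and nurse practitioner". The look-back is "in the past 6 months (at baseline) and past 3 months (follow-ups". The outcome is labelled as initiation in the period after the intervention.

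**Analysis (Analytic Plan, Overview).** The binary outcome is analysed with a categorical latent growth model and with simple logistic regression at each time point. The only covariates mentioned are demographic and military characteristics that differ between the arms at baseline.

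**The concern.** Initiation means moving from no care to care. The follow-up item captures the second half of that: care in the last 3 months, whether new or continuing. The first half rests on the entry screen. The screen asks about appointments for behavioral health treatment. The outcome item prompts with support groups, medications and general medical providers. A prompted list can draw a yes that a question about appointments misses.

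A participant in a provider-led group not thought of as an appointment, or whose long-running medication is handled at general medical visits, could pass the screen and then report that same care at 3 months. Counting the first yes after randomization does not help by itself, because the first yes would be the continuing care.

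At stake are the meaning of the reported initiation rate, which would be partly a continuation rate, and some power for a primary outcome.

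**Working it through.** **1. Screen and outcome item side by side**

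| Feature | Entry screen | Outcome item |
|---|---|---|
| Unit | Appointment, recent or upcoming | Having seen a provider |
| Concern | Behavioral health | Alcohol, substance use or mental health |
| Setting | VA or elsewhere | VA or non-VA |
| Kinds of care prompted | None described | Five, including support groups and medications |
| Providers prompted | None described | Mental health, general medical, addiction |
| Window | Past 6 months, and future | 6 months at baseline, 3 months at follow-up |

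Concern and setting agree. The unit and the prompts do not. Nothing states what a yes at baseline does to the scoring of a later yes.

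**2. Is there a stated figure to reproduce?** None for initiation. The Power Analysis section gives detectable effects for continuous outcomes only. At 80% power and two-sided 5%, d = 0.22 implies n = 2 × ((1.960 + 0.842) / 0.22)² ≈ 324 per arm, or about 81% of 400. I use 324 as the number analysed at 3 months. No attrition rate is stated, so this is an inference.

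**3. Dilution formula.** Let q be the share of each arm already in care that passes the screen and answers yes at follow-up. With true initiation p among the rest, the observed rate is p′ = q + (1 − q)p. The risk difference becomes (1 − q)(p₁ − p₀), so it shrinks by the factor (1 − q) and the odds ratio moves toward 1. Randomization makes q equal in the two arms in expectation.

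**4. Illustration.** Assumed, and not in the article: p₀ = 10%, p₁ = 18%, and the values of q. Power = Φ[(Δ − 1.96·s₀) / s₁], where s₀ is the standard error under the pooled rate and s₁ the unpooled one, with n = 324 per arm. For q = 5%:
- p₀′ = 0.05 + 0.95 × 0.10 = 0.145; p₁′ = 0.05 + 0.95 × 0.18 = 0.221; Δ = 0.076
- s₀ = 0.0304, s₁ = 0.0302
- power = Φ[(0.076 − 0.0595) / 0.0302] = Φ(0.54) = 71%

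| q | Observed rates | Difference (points) | Power, all randomized | Share of control events that is prior care (q / p₀′) | Power, baseline-no only, n(1 − q) per arm |
|---|---|---|---|---|---|
| 0 | 10.0% vs 18.0% | 8.0 | 84% | 0% | 84% |
| 2% | 11.8% vs 19.6% | 7.8 | 78% | 17% | 83% |
| 5% | 14.5% vs 22.1% | 7.6 | 71% | 34% | 82% |
| 10% | 19.0% vs 26.2% | 7.2 | 59% | 53% | 80% |

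The last column assumes that the baseline item identifies everyone in q, so it is an upper limit on what the restriction recovers.

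**5. Sensitivity to the assumed effect.** With 25% versus 50%, power stays above 99% for q up to 20%, even at 297 per arm. The 50% is the article's 12-month hypothesis for the intervention arm; the 25% is assumed. With 10% versus 20% and 325 per arm, power is 95%, 87% and 77% at q = 0, 5% and 10%.

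**The case against.** The case that little is wrong has several parts.

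- **The screen is defined by concern and covers any setting.** The Background section uses "behavioral health care (ie, care for mental health or substance use disorders", which does not depend on provider type. A primary care visit made for depression is already excluded. This stands. A reader might infer that primary care lies outside the screen altogether; the text does not support that.
- **The outcome requires having seen a provider.** Medication without a visit, or a group led only by peers, does not clearly count. This largely stands, although the item's own example of attending groups to stay abstinent leaves room for a yes. What remains is provider-led groups, general medical visits that also cover medication, and people who answer the screen and the prompted item differently.
- **The growth model can take in the baseline response.** This stands. The point therefore falls mainly on the logistic regressions at each time point.
- **How to code a baseline yes may sit in an analysis plan that is not shown.** Fair. The silence alone would be no finding. But the article itself fixes an item that records any care, labels it initiation, and pairs it with a differently worded screen.
- **The power figures rest on assumed inputs.** Correct. They show direction and rough scale and are not evidence about this trial. A reader might take the 5% and 10% rows as expected values; nothing in the article supports any particular share.

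**Conclusion.** The mismatch is real but narrow. The screen and the outcome item ask different questions, a follow-up yes does not separate new from continuing care, and the logistic regressions have no stated use of the baseline answer. Participants who pass the screen yet answer yes at baseline can be counted as initiators.

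The expected consequence is non-differential attenuation and some lost power on one of the primary outcomes. A reader might infer that the trial would favour one arm. It would not, because the baseline survey precedes randomization and prior care should balance.

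The size cannot be determined from the article. The loss is negligible if the true effect is very large. For a difference of 8 points from an assumed low control rate, 2% to 5% leakage would cost about 6 to 13 percentage points of power. Whatever the power, the reported initiation rate would include some continuing care. Low to moderate priority.

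**What to change.** Add a sentence to the analytic plan: treatment initiation is analysed as the first yes after randomization among participants who answered no to the same item at baseline, with the all-randomized analysis, adjusted for the baseline answer, reported alongside. The baseline survey is completed before randomization, so the restricted comparison remains randomized. Report the number answering yes at baseline in each arm.

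If screening is still open to edits, bring the screen's wording into line with the outcome item.

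The cost is small. The item is already collected, and only this one analysis loses a few participants. The restriction has a limit that should be stated: it will not catch ongoing care with no provider visit in the 6 months before baseline, such as medication reviewed once a year. That person truthfully answers no at baseline and could still be scored as an initiator.

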#### Secondary Outcomes

The decision to seek care and then actual receipt of care can be a lengthy process. Given that participants may not receive any care during the 12 months of follow-up, we will also assess their readiness to receive care in the future and if they made preparations to receive that care. Preparatory behaviors will be specified as 6 behaviors participants would definitely do, probably do, probably not do, or definitely not do in the next 30 days to prepare for treatment (ie, looking at options on the internet; discussing with a partner, family member, or friend the options available; talking with a partner, family member, or friend about their experiences with treatment; contacting a provider to learn more about the options; contacting the insurance provider to see what options are available; and contacting a provider to make an appointment). Two readiness rulers will also assess participants’ readiness to seek care in the next 30 days in order to reduce their drinking and to address any mental health concerns they have from 0 (not ready at all) to 10 (absolutely ready).

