### This Study

To build upon the pilot trial, we designed this study to test the longer-term effects (ie, 12-month outcomes) of a brief PNF intervention on drinking and treatment (ie, motivation and preparation for; actual initiation) outcomes. For this larger study, we expand upon the original pilot intervention content, which primarily focused on correcting misperceived norms of veteran peer alcohol use, to include empirically informed approaches to increase motivation to address one’s alcohol use and co-occurring behavioral mental health problems (eg, depression, anxiety, and PTSD) in more formal care settings (ie, those beyond a one-time brief intervention such as care with a provider at a VA). In doing so, we will evaluate intervention effects on readiness to initiate behavioral health care, preparatory behaviors toward seeking that care, and any actual care initiation in the postintervention period. To evaluate the impact of the intervention on these outcomes, we intend to enroll and randomize 800 participants into either the PNF intervention (n=400) or a resources-only control condition focused on providing information related to care services (n=400). In the protocol that follows, we describe our recruitment methods and target sample, list our measures for outcomes and moderators of intervention effects, discuss the intervention content in detail, and lay out the proposed analytic plan to examine the efficacy of the brief internet-based intervention on alcohol use and treatment initiation outcomes.

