### Specific Aims and Hypotheses

For the first aim, we intend to conduct an RCT of the BRAVE intervention by randomly assigning veterans with potentially hazardous drinking patterns, but who have not received recent treatment for drinking or any other behavioral health problem, to receive either the BRAVE intervention or a resources-only control condition. We hypothesize that BRAVE participants will drink less (fewer days per week, fewer drinks per occasion, and fewer binge drinking days), experience fewer negative alcohol-related consequences, and report more treatment readiness, preparatory behaviors, and initiation behaviors at 3, 6, 9, and 12 months post intervention, relative to control participants. For the second aim, we will determine for which subgroups the intervention works best. We hypothesize BRAVE participants who report more baseline barriers to care (eg, perceived public stigma beliefs that others would view them negatively for seeking care, not having time due to work or family responsibilities), baseline high levels of PTSD or depression symptoms, and higher baseline problematic alcohol use will benefit most from the intervention in terms of drinking reductions and treatment initiation outcomes. Sex (male and female) will be examined as an exploratory moderator, which expands on veteran work that traditionally examines male veterans only, which is important considering unique female-specific factors that affect treatment engagement [39].

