### Analytic Plan

#### Overview

Prior to the main aims analyses, we will assess for multivariate normality. The maximum likelihood estimator will be used if data are approximately normal and robust maximum likelihood will be used if the data are not multivariate normal. Missing data will be assumed to be missing at random and handled using direct maximum likelihood techniques. We will assess for differences in baseline demographics and military characteristics between the intervention (BRAVE) and control conditions. Any characteristic significantly different between groups will be controlled for in analyses.

To assess the effects of the intervention on continuous primary outcomes (drinking days, average drinks per occasion, binge drinking days, negative alcohol-related consequences, and treatment initiation) and secondary outcomes (preparatory behaviors, readiness to seek care ruler for alcohol, readiness to seek care ruler for mental health), a taxonomy of latent growth models will be estimated [75]. The primary outcome time point for this trial will be the baseline to first follow-up (ie, 3 months post baseline); however, we are interested in the past 30-day changes from baseline to each of the 3 additional follow-up timepoints (ie, baseline to 6, 9, and 12 months post baseline). To assess between-group differences in the intercept and growth factors, we will regress each on a dummy variable representing the intervention (BRAVE=1) and control (control=0) groups. For any count variables, negative binomial or Poisson distributions will be explored for better model fit. To understand the change in treatment initiation (binary outcome), we will use latent growth models with categorical outcomes, as well as estimate simple logistic regression at each time point. To understand the practical significance, we will calculate standardized mean differences (Cohen *d*) at all 4 follow-up time points for both between group and within group.

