#### Power Analysis

Given this study design (and standard *P*<.05; 2-tailed testing), we will have 80% power to detect small treatment effects between the groups; specifically, effects of d=0.22 at 3- and 6-month follow-ups and d=0.23 at 9- and 12-month follow-ups. For reference, our observed intervention effect sizes at 1 month post intervention in the pilot study were *d*=0.17 for average drinks, *d*=0.18 for binge days per month, and *d*=0.19 for consequences [49]. We have similarly found small effect sizes over 2 years of follow-up in other large-scale PNF studies [76-78]. We expect effect sizes to be small, though slightly larger than those in our prior work given we include a sample screening positive for hazardous alcohol use that could benefit from treatment, whereas prior work targeted general college students and young veterans drinking at less severe levels. As noted, given that this intervention targets those who may never have received care otherwise, small effects seen in brief interventions, such as this, are potentially clinically significant.

Our prior work evaluating treatment-seeking behaviors has found rates of preparatory and actual treatment-seeking by service members to increase by double following brief phone-based feedback [79]. Other work has similarly found rates of substance use treatment initiation to increase to upwards of 50% following in-person feedback–based approaches [80]; thus, we hypothesize that upwards of 50% of participants who receive the enhanced PNF will report actual treatment initiation at some point during the 12-month follow-up period. We will examine preparatory behaviors (ie, steps along the way to actual initiation) and motivation to seek care.

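### Preparatory behaviors are measured as intentions for the next 30 days, so the Aim 1 hypothesis about preparatory behavior cannot be answered by its own measure

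*Protocol article*

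**What the plan says.** All references are to the protocol article.

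- **Secondary Outcomes, purpose.** Because care may not start within 12 months, "we will also assess their readiness to receive care in the future and if they made preparations to receive that care".
- **Secondary Outcomes, definition.** The next sentence specifies preparatory behaviors as six "behaviors participants would definitely do, probably do, probably not do, or definitely not do in the next 30 days to prepare for treatment". The six cover searching for options, conversations with people close to the participant, and contacts with a provider or insurer.
- **Secondary Outcomes, rulers.** "Two readiness rulers will also assess participants’ readiness to seek care in the next 30 days", one for drinking and one for mental health, each scored 0 to 10.
- **This Study.** The effects to be evaluated are on "readiness to initiate behavioral health care, preparatory behaviors toward seeking that care, and any actual care initiation in the postintervention period".
- **Specific Aims and Hypotheses.** BRAVE participants are expected to "report more treatment readiness, preparatory behaviors, and initiation behaviors at 3, 6, 9, and 12 months post intervention".
- **Analytic Plan, Overview.** The models cover "secondary outcomes (preparatory behaviors, readiness to seek care ruler for alcohol, readiness to seek care ruler for mental health), a taxonomy of latent growth models".
- **Power Analysis.** "We will examine preparatory behaviors (ie, steps along the way to actual initiation) and motivation to seek care".

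**The concern.** Two adjacent statements in Secondary Outcomes do not agree. The purpose is phrased in the past tense, as preparations already made. The response scale asks about the future, and about likelihood rather than fact. A participant who answers that they would definitely contact a provider has told the trial nothing about whether they did.

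The article builds a three-step sequence: being ready, preparing, starting care. With these items the middle step is not observed. The first step is measured in two ways, once by the rulers and once by the six intention items, all over the same 30 days ahead.

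What is at stake is the reading of the result. A difference between arms on the six items would be reported under the name of a behavior, and could be taken as evidence that BRAVE moved people to act. Conversely, a real increase in preparatory action could be missed because nobody was asked about it.

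**Working it through.** No figure in the article depends on this point, so the check sets the sections side by side and then compares time windows.

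**Step 1. Construct against measure.**

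- Purpose (Secondary Outcomes): preparations made. Tense: past. Type: action.
- Items (Secondary Outcomes): what participants would do, on a four-level scale from definitely to definitely not. Tense: future. Type: intention.
- Rulers (Secondary Outcomes): readiness over the next 30 days. Tense: future. Type: motivation.
- Initiation (Primary Outcomes): whether a provider was seen in the past 6 months (baseline) or past 3 months (follow-ups). Tense: past. Type: action.

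The article does use past-tense reporting where it wants behavior, as the initiation item shows. The preparatory items do not follow that pattern. They match the rulers in tense and window.

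**Step 2. How the rest of the article uses the outcome.**

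- This Study lists readiness, preparatory behaviors and initiation as three separate things.
- Specific Aims and Hypotheses predicts more of each of the three in BRAVE.
- Power Analysis describes preparatory behaviors as intermediate steps toward care. It also refers to prior work in which rates of preparatory and actual treatment-seeking doubled after brief phone feedback. A mean on an intention scale cannot be set against such rates.

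All three uses need a record of actions taken.

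**Step 3. Which period the items cover.** Suppose intention were accepted as a stand-in for action.

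- Surveys are at baseline and 3, 6, 9 and 12 months. The Procedures section places the baseline survey before randomization, so its answers cannot reflect the intervention.
- Post-randomization answers look ahead over months 3 to 4, 6 to 7, 9 to 10 and 12 to 13.
- The last window lies after the end of follow-up. Within follow-up, 3 × 30 = 90 days are covered, and 90/365 is about 25% of the year.
- No post-randomization answer covers the first 3 months. The BRAVE Intervention Condition section prompts goals for the next day and the following days and weeks, and the Analytic Plan makes 3 months the primary time point.
- A past-3-month item at the four follow-ups would cover 4 × 3 = 12 months, the whole of follow-up, as the initiation item already does.

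**Step 4. Extent.** The Analytic Plan lists three secondary outcomes: preparatory behaviors and two rulers. The rulers are labelled as readiness and measure readiness. One of the three is mislabelled.

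**The case against.** **The article is a condensed report.** The full questionnaire could contain past-tense items. This would carry weight if the article were silent. It is not silent: it says how preparatory behaviors will be specified, and that specification is prospective. An unseen document could add items, but the definition printed here would still be wrong for the stated purpose.

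**Intention is worth measuring.** It is, and the items need not be discarded. This supports relabelling them. It does not support calling them behavior.

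**Only a secondary outcome is touched.** This stands. Actual initiation and the drinking outcomes are measured separately, and Aim 1 does not fail as a whole.

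**A stronger reading.** A reader might infer that participants who have already entered care will answer low on the forward-looking items because nothing is left to seek, so that success on initiation would be scored as failure and would count against BRAVE. The documents do not support going that far:

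- The outcomes are grouped with the continuous ones and no success cut-off is defined, so nobody is scored as a failure.
- Low answers from people in care are a conjecture. Initiation can be a single visit, to a general medical provider among others, and the Background notes that many veterans are seen only once or twice. Such a person may still have care to seek.
- Someone in care for mental health may have alcohol care still ahead, and someone in care may equally report being fully ready.
- The hypothesized 50% in Power Analysis is cumulative over 12 months, not the share in care at one survey. The article gives no control rate and no scores by care status, so no size can be derived.
- How participants in care are asked or scored is a detail that an article may leave to the full protocol or analysis plan.

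What remains is a caution. Eligibility excludes recent and upcoming appointments, so being in care arises after randomization and may differ by arm.

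**Conclusion.** The point holds as a mismatch between a stated construct and its measure. As described, the trial cannot show whether participants prepared for care; it can show whether they say they intend to. The preparatory-behavior part of Aim 1 therefore cannot be answered, and following the plan would report intention as behavior.

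The extent is one of three secondary outcomes. No sample size, power figure or primary outcome changes. The conclusion rests only on the wording in the article and assumes that the items are fielded as described there.

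The documents do not establish that participants in care will score low, or that the BRAVE effect on these outcomes would be diluted or reversed. That possibility is a reason for care in interpretation and is not part of the finding.

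**What to change.** 1. At baseline and each follow-up, ask the same six items as done or not done over a fixed past window. The past 3 months at follow-ups would match the initiation item and leave no gaps. Using the same length at baseline keeps the counts comparable across waves.
2. Analyse the count done (0 to 6) as the preparatory-behavior outcome. The Analytic Plan already provides for count distributions.
3. Keep the current six items under the name *intention to prepare*.
4. If the surveys are already fielded, rename the outcome in the secondary outcome list and limit that part of Aim 1 to intention.
5. When reporting the intention items and the rulers, show them alongside initiation status. Do not give participants in care the top score by rule, because that would partly copy the primary initiation outcome into the secondary ones.

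The cost is six short items per survey, slightly longer surveys and a few lines of wording. Under item 4 only the wording changes, but the behavior question then stays unanswered.
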